#### Muscle architecture

The muscle architecture (fascicle length, pennation angle, and muscle thickness) of MG muscle of dominant limb will be assessed using an ultrasound (Konica Minolta Medical Imaging Inc [name], Wayne, NJ, USA) in B mode with linear arrangement transducer (4 cm height x 2 cm length, 10 MHz), with the depth adjusted to 4 cm for the MG.

The image of MG will be performed with the participant resting in the prone position, with the feet hanging from the edge, and an ankle joint angle at 15° dorsiflexion will be fixed. The ultrasound transducer will be positioned at 30% of the portion between the fibula’s lateral malleolus and the lateral condyle of the tibia [25]. The transducer will be oriented in the axial plane, aligned perpendicularly to the muscle, and moved from the center to the lateral position along with templates demarcated on the skin.

It is important to highlight that the gastrocnemius muscle is essential to maintain independence, gait speed and reduce falls risk. However, the aging process causes a muscle architecture alteration, reducing the cross-sectional area, pennation angle, and fascicle length. These age-related alterations resulting in a reduction of strength and muscle power, gait speed and functionality [26].

### Secondary outcomes

#### Gait

The gait will be analyzed through the instrumented walking monitor ProtoKinetics Zeno Walkway (ProtoKinetics LLC, Havertown, Pennsylvania). The evaluation protocol will consist of four patterns: walking at the usual speed, maximum speed, the usual speed with a dual-task, and maximum speed with a dual-task for a distance of 10 meters. Dual-task gait will be assessed using an arithmetic cognitive task (countdown from 50) [27].

The parameters will be analyzed: gait speed (m/s), cadence (steps/min), stride time (secs), stride length (m), stride width (m), single and double support time (secs), and swing time (secs). Besides, the walk ratio (WR) will be obtained by dividing step length by cadence [28], and the locomotor rehabilitation index (LRI) is calculated as the percentage ratio between self-selected speed and optimum speed (algebraically LRI = 100 × self-selected speed/optimum walking speed) cc.

#### Physical function

The physical function will be assessed using the Short Physical Performance Battery Test [29] and the Senior Fitness Test [30], aiming to verify muscle strength, agility, and dynamic and static balance. The Short Physical Performance Battery Test is composed of tandem, semi-tandem, side-by-side stands balance test, 4-meters walking speed test, and 5-times sit-to-chairs stand test. The Senior Fitness Test is composed of 5 times sit to chair stand test, arm curl test (number within 30 seconds), chair sit and reach test (distance between fingers and toe), back scratch test (distance between the two third fingers), Timed-up-and-go (time to rise, walk 3 m and return to the chair) and 6-minute walk test (distance walked in 6 minutes).

#### Quality of life

Quality of life will be assessed using the Medical Outcomes Study 36-item Short-Form Health Survey (SF-36) [31]. The SF-36 comprises 36 questions that cover eight health domains: physical limitation because of health problems, social limitation because of physical or emotional problem, usual role activities limitation because of physical health or emotional problems, body pain, general mental health, vitality, and general health perceptions.

#### Physical activity level and exercise intensity control

The physical activity level and the control of the exercise intensity will be evaluated using an accelerometer (Actigraph brand, model GT3X). To analyze the physical activity level, participants will be instructed to use the device for seven consecutive days, all day long, withdrawing only to sleep and to perform water activities, including bathing [32]. The accelerometer will be attached to the ankle of the dominant leg, just above the malleolus. It will be considered valid data the use of the accelerometer for at least four days, where at least one day has to be recorded during the weekend. The day will be considered valid when at least 10 hours are recorded. The data will be collected at a frequency of 60 Hz. The process of downloading and analyzing data will be carried out by the Actilife software using the Freedson equation [32].

The exercise intensity will be controlled by the use of accelerometers during the exercise sessions. The analyzed variable will be the average calories spent per day and session, sedentary time, light, moderate, vigorous, and very vigorous activities.

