### Intervention groups

Volunteers will participate in a multicomponent exercise program combining supervised and home-based exercise for 12 weeks, three times per week, 60 min per session. Participants will be divided into (1) supervised exercise (SUP), who will attend supervised group sessions at the training center; (2) home-based exercise (HB), who will participate in individual sessions at home; (3) supervised plus home-based exercise (SUP+HB), who will attend to one session per week at the training center and two sessions per week at home. Physical educators or physiotherapists will guide the supervised sessions at the training center.

The volunteers who will attend home sessions (HB and SUP+HB) will have an initial visit to their home to receive recommendations about how to perform the exercises safely. A guide with illustrations and instructions to reinforce proper exercise execution will be provided to each participant with space for recording the sessions performed and possible occurrences. On this occasion, they will receive ankle cuff weights (1, 2 and, 4 kg) to the strength training and a square stepping for walking exercises. To control program adherence, participants will record the days they complete the program, and they will also receive messages with incentives to perform the exercises at home.

The exercise program will consist of functional exercises of muscle strength, balance, flexibility, and gait, based on the recommendations of Singh et al. [16] and American College of Sports Medicine [17] (ACSM). Each session will be divided into 05 minutes of dynamic and articular warm-up, 10 minutes of dynamic and static balance exercises, 25 minutes of muscle-strengthening exercises, 10 minutes for gait exercises, and 10 minutes of flexibility exercises.

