The exercise program will consist of four phases: phase 1 (1 to 3 weeks), phase 2 (4 to 6 weeks), phase 3 (7 to 9 weeks) and, phase 4 (10 to 12 weeks). Each phase will differ in the load and difficulty level of exercises, as shown in Table 1. The session intensity will be measured by the rate of perceived exertion (RPE) according to Borg Scale (6–20). In all groups analyzed, an explanation regarding the scale will be provided as well as a familiarization with the protocol before the start of interventions. Those measurements will be analyzed in different moments of the session, aiming to characterize the intensity perceived. In all training sessions, the volunteers will be encouraged to perform the exercises respecting the 1:3 ratio for strength exercises[18].

**Table 1 pone.0259827.t001:** Multicomponent exercise program planning.

Modality	Balance Training	Resistance Training	Gait Training	Flexibility Training
**Volume**	1–2 sets of 4–5 different exercises emphasizing static and dynamic postures for 30 seconds	**Phase 1:** 3 sets of 12 repetition, 1-min interval between sets **Phase 2**: 3 sets of 10 repetition, 30-s interval between sets **Phase 3:** 3 sets of 8 repetition, 1-min interval between sets **Phase 4**: 3 sets of 8 repetition, 30-s interval between sets.	1 set 5 repetition 6 gait exercises	Sustain stretching exercises for 20 sec to each major muscle groups
**Intensity**	Progressive difficulty with increases in complexity **Phase 1:** reduction of foot support base. **Phase 2**: unstable surface. **Phase 3:** reduction of visual information. **Phase 4:** objects manipulation.	**Phase 1:** 13–15 on the Borg Scale. **Phase 2 to 4**: 15–17 on the Borg Scale.	**Phase 1 to 4:** 12–13 on the Borg Scale (40–60% of heart rate reserve)	**Phase 1 to 4:** Progressive neuromuscular facilitation technique, which involves stretching as far as possible, then relaxing the involved muscles, then attempting to stretch further, and finally holding the maximal stretch position for at least 20 seconds.

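### An ankle-worn accelerometer is scored with the Freedson equation and its intensity bands without any ankle calibration, so walking is probably over-scored and feet-planted strength work barely registers

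*Protocol article*

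**What the plan says.** The section on physical activity level and exercise intensity control names one device for both purposes, "evaluated using an accelerometer (Actigraph brand, model GT3X", one wear site, "The accelerometer will be attached to the ankle of the dominant leg, just above the malleolus", and one scoring rule, "analyzing data will be carried out by the Actilife software using the Freedson equation [32". The outputs are fixed: "The analyzed variable will be the average calories spent per day and session, sedentary time, light, moderate, vigorous, and very vigorous activities". The same section extends accelerometry to the training itself: "The exercise intensity will be controlled by the use of accelerometers during the exercise sessions". It mentions no ankle-specific cut-points, no conversion between sites and no validation at the ankle.

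Four other places bear on the point.

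- The Introduction makes session intensity, volume and density by modality one of the two study objectives.
- Intervention groups measures session intensity by the Borg scale (6-20) in all groups. Table 1 sets gait work at "12–13 on the Borg Scale (40–60% of heart rate reserve" and strength work at Borg 13-15 in phase 1 and 15-17 from phase 2.
- Intervention groups says of participants with home sessions: "they will receive ankle cuff weights (1, 2 and, 4 kg) to the strength training".
- The Discussion lists spontaneous activity, including getting to the training site on foot or by transport, as a limitation that accelerometry will monitor but the trial will not control.

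**The concern.** An activity band is a fixed count threshold, and it means what it says only at the body site for which it was set. The ankle swings with every step and stays nearly still when the feet are planted. A threshold set elsewhere on the body can therefore put the same walking in a different band. The article fixes both the site and the rule, so this is a stated measurement choice and not a detail left to another document.

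At stake are the only accelerometer variables that the article analyses. They are its only device-based evidence on the intensity objective and on travel-related activity. If walking is over-scored and walking differs by arm, the per-day contrasts between arms carry a bias and not only shared noise. If planted-feet strength work is nearly invisible to the sensor, the session bands say little about a part of the session where supervision is expected to matter.

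**Working it through.** The article gives no count threshold, calibration coefficient or expected accelerometer difference, so there is no stated figure to reproduce. The check has three parts.

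**1. Walking and the band thresholds (illustrative; all inputs assumed)**

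- k = ankle count divided by waist count in walking. The documents do not give it.
- M = the moderate cut-point; the vigorous cut-point is rM, with r = 2.5 to 3.
- True waist-equivalent walking counts are spread evenly within each band; the upper-light band runs from 0.3M to M.

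A threshold T is crossed at the ankle once the waist-equivalent count exceeds T/k. Hence:

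- share of upper-light time scored moderate or higher = (1 − 1/k) / 0.7;
- share of moderate time scored vigorous or higher = (r − max(1, r/k)) / (r − 1).

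| k | Upper-light moved up | Moderate moved up, r = 3 | Moderate moved up, r = 2.5 |
|---|---|---|---|
| 1 | 0% | 0% | 0% |
| 1.2 | 0.167/0.7 = 24% | 0.5/2 = 25% | 0.417/1.5 = 28% |
| 1.5 | 0.333/0.7 = 48% | 1/2 = 50% | 0.833/1.5 = 56% |
| 2 | 0.5/0.7 = 71% | 1.5/2 = 75% | 1.25/1.5 = 83% |
| 3 | 0.667/0.7 = 95% | 100% | 100% |

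**2. Exposure by arm**

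Intervention groups sets three sessions a week. SUP trains at the centre, SUP+HB attends it once a week, and HB trains at home. That gives 3, 1 and 0 centre trips a week. Any part of those trips made on foot enters the per-day calories and bands in that proportion. The article gives neither the share of travel on foot nor its duration, so the between-arm bias cannot be sized.

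**3. Strength exercises with the feet planted (counted from Table 1)**

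- Phases 1-2, 17 listed: sit-to-stand, pelvic lift, wall sit, barbell curl, row, front raise and sit-up. That is 7/17 = 41%, or 9/17 with the two ankle plantar-flexion exercises.
- Phases 3-4, 19 listed: wall sit, barbell curl, dumbbell row, sit-up, squat, pelvic lift, bent-over row, dumbbell curl, lateral raise and stiff-legged deadlift. That is 10/19 = 53%, or 11/19 with the calf raise.

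Strength work takes 25 of 60 minutes (41.7%) and gait 10 of 60 (16.7%). From phase 2, strength is prescribed at a higher Borg level than gait, yet about half or somewhat less of its listed exercises produce little movement at the sensor. This part does not depend on where the equation was calibrated.

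**The case against.** The strongest objection is that the article nowhere says the Freedson equation is a waist calibration, and the reference cited for it is not available here. This stands: the over-scoring of walking is conditional on that property of the named equation. It does not remove the point, because the article fixes an ankle site and a named equation and shows nothing to support the pairing. Nor does the condition touch the planted-feet argument.

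Session intensity is also already measured by Borg rating in every arm. This stands too and limits the damage. But the article also says that accelerometers control session intensity, and it does not say which measure decides the comparison between arms.

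Several stronger readings are tempting but unsupported:

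- *The scores contradict Table 1, or strength work is largely scored sedentary or light.* The documents contain no counts to show this. Many listed exercises, such as lunges, knee flexion and extension, hip abduction and step-ups, move the ankle and could score high.
- *SUP participants walk to the centre, so their activity is inflated.* The Discussion leaves travel mode open between walking and transport, and SUP+HB travels as well. Within sessions the exercise content is common to all arms, so mis-scoring there is partly shared.
- *The cuff weights displace the sensor.* The ankle sentence follows the seven-day wear instruction. Ankle wear during sessions is an inference, and nothing says that the two cannot be worn together.
- *Waist wear cures everything.* It would not capture curls or wall sits either.

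**Conclusion.** The point holds in conditional form. The article applies the Freedson equation and fixed intensity bands at the ankle with nothing to show that they are valid there. On the assumption of a waist calibration, walking is likely to be over-scored. The amount ranges from nothing at k = 1 to about 48-83% of upper-light and moderate walking time moved up a band at k = 1.5 to 2, given the even spread and cut-point ratio assumed above. Those figures illustrate sensitivity; they do not estimate the error in this trial.

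Per-day calories and bands would be affected unequally across arms to the extent that centre trips are made on foot. Independently of calibration, the bands are a poor intensity measure for the feet-planted part of the strength block, assuming that the device is worn at the ankle in sessions. The primary outcomes, the sample size and the Borg ratings are unaffected. The problem is therefore confined to the accelerometer variables and what they contribute to the intensity objective, but it is worth correcting.

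**What to change.** In the section on physical activity level and exercise intensity control, state the site for which the equation is calibrated and the site used during sessions, then do one of two things:

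1. wear the device at the waist, so that site and equation match; or
2. keep the ankle and replace the Freedson bands and calories with mean counts (vector magnitude), or with cut-points calibrated for the ankle in older adults.

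With either choice, name the Borg rating already collected in all arms as the between-arm measure of session intensity, and limit accelerometry to ambulatory activity. This second step is needed because a change of site alone leaves static and upper-limb strength work uncaptured.

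The cost is a wording change plus a different strap position or software setting, with no new device or visit. The downside is small: data already recorded at the ankle must be re-scored and cannot be compared with published Freedson minutes.

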To the best of our knowledge, this is the first study that aimed to analyze the neuromuscular mechanisms responsible for improvements in muscle strength and physical function in older adults with the addition of supervised sessions in home-based programs compared to totally unsupervised (home) and supervised training. Thus, we hypothesize that the addition of supervised sessions in home-based programs will lead to greater improvements in neuromuscular mechanisms due to the higher control over the training variables when compared to home-based programs. Besides, we believe that the addition of supervised sessions in home-based programs will provide similar neuromuscular benefits compared to fully supervised training interventions.

Therefore, understanding the influence of different exercise supervision levels on neuromuscular mechanisms and how it may change muscle strength and physical function seems essential for planning coherent exercise programs for older adults, expanding training strategies for that population. Thus, this study had two objectives: Compare the effects of a multicomponent exercise program in different application modalities (supervised vs. home vs. supervised+home) in neuromuscular adaptations, muscle strength, gait, physical function, and quality of life of older adults; and analyze the session intensity, volume, and density of different training modalities (supervised vs. home vs. supervised+home) s in community older adults.

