**Fig 2 pone.0259827.g002:**
[figure not shown]
Representation of the timeline and assessments of the study.

All participants visited the laboratory on two nonconsecutive days with a minimum of 48 hours of resting to perform baseline evaluations. In the first visit, participants will be requested to answer a clinical anamnesis, followed by an anthropometric assessment. All protocols applied for primary and second outcomes will be described below.

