### Primary outcomes

#### Muscle isokinetic strength

The evaluation of muscle isokinetic strength will be performed using the Biodex Multi-joint System dynamometer (Biodex Medical Systems. Inc. Shirley. NY. USA). The protocol includes two sets of three repetitions of the knee, hip, dorsiflexion, and plantarflexion concentric flexion/extension movements at 60°/s and 180°/s of dominant limb, with a two-minute interval between sets [19]. Participants will be positioned following the Biodex factory specifications, which are described by Symons et al. [20].

Each test will be performed twice at the same evaluation session, with different verbal commands of the evaluator: in the first test, a submaximal set will be used for familiarization, followed by a second test, which will be held with maximum strength for the record. Data will be acquired at 1000 Hz, and all muscle strength tests will be analyzed using the Biodex System 3 Advantage software, version 3.2. The variables analyzed will be peak torque/body weight, total work, and average power.

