### Sample size

The sample size calculation was made using the G*Power software (version 3.1) [33]. A priori analysis was performed with the following input parameters: effect size (0.25) [7], type I error (0.05), type II error (0.95), number of groups (3), number of measurements (3), and a correlation between group (0.5). Also, the loss rate of 20% was considered. Thus, our analysis revealed a sample size of 66 subjects, divided into three groups of 22 participants.

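### Session calories are to be compared between arms with no allowance for body mass, which costs precision and lets chance weight imbalance into the contrast

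*Protocol article*

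**What the plan says.** The protocol article, under physical activity level and exercise intensity control, gives the purpose of the session accelerometry: "The exercise intensity will be controlled by the use of accelerometers during the exercise sessions". It then names what is analysed: "The analyzed variable will be the average calories spent per day and session", followed in the same sentence by sedentary time and four bands of activity. No division by body mass and no mass covariate is mentioned.

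The variable serves the second of the two objectives in the Introduction, to "analyze the session intensity, volume, and density of different training modalities". It is not the only measure of intensity. Under Intervention groups the article also states: "The session intensity will be measured by the rate of perceived exertion (RPE) according to Borg Scale".

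Statistical methods compares groups and periods (pre and post) by mixed ANOVA. It brings in ANCOVA only when the groups are seen to differ at baseline, and names no covariate. Body weight is needed elsewhere, because for isokinetic strength "The variables analyzed will be peak torque/body weight, total work, and average power". The first baseline visit includes a clinical history "followed by an anthropometric assessment".

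**The concern.** The energy cost of a given movement rises with body mass. That is general physiology and is not stated in the document. Two people who do the same session with the same effort can therefore record different calories because one is heavier. Men and women over 60 are eligible, and allocation is by blocks with no stratification stated, so mass will vary between people and by chance between arms.

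For an outcome measured before and after training, a stable body-size effect largely cancels in the change. Exercise sessions do not exist before training, so nothing cancels. The comparison of session calories between arms then carries body-size variation that has nothing to do with supervision. This is noise in the comparison meant to show whether supervision changes what people do in a session.

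**Working it through.** **Inputs from the document.** Arm size is 22, from "a sample size of 66 subjects, divided into three groups of 22 participants". The article gives no figure for calories, kcal/kg or body mass, so there is no stated result to reproduce for this variable. The sample size does not depend on it. With the listed inputs (f = 0.25, alpha 0.05, power 0.95, 3 groups, 3 measurements, correlation 0.5) a group-by-period F test needs 54. Allowing for 20% loss gives 54 × 1.2 = 65 or 54/0.8 = 68, close to the stated 66.

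**Assumptions.** The coefficient of variation (CV) of body mass, CVm, is 0.12-0.20. The CV of kcal/kg, CVk, is 0.15-0.30. Calories = mass × kcal/kg, with the two independent.

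**Step 1: chance mass imbalance between two arms.** The SD of the difference, as a share of mean mass, is CVm × √(2/22) = CVm × 0.3015.
- CVm 0.12: 3.6%; × 1.96 = 7.1%
- CVm 0.18: 5.4%; × 1.96 = 10.6%
- CVm 0.20: 6.0%; × 1.96 = 11.8%

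Under proportionality the same percentage appears in mean session calories.

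**Step 2: variance.** CVraw² = CVm² + CVk² + CVm²·CVk². Inflation = CVraw²/CVk². Equivalent arm size on the kcal/kg scale = 22/inflation.

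| CVm | CVk | CVraw² | Inflation | Equivalent n per arm |
|---|---|---|---|---|
| 0.12 | 0.30 | 0.0144 + 0.0900 + 0.0013 = 0.1057 | 1.17 | 18.7 |
| 0.18 | 0.20 | 0.0324 + 0.0400 + 0.0013 = 0.0737 | 1.84 | 11.9 |
| 0.20 | 0.15 | 0.0400 + 0.0225 + 0.0009 = 0.0634 | 2.82 | 7.8 |

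**Step 3: power for a 20% difference between two arms.** This uses the normal approximation, two-sided 5%, one comparison, no Bonferroni correction. Power = Φ(0.20/(CV × 0.3015) − 1.96).
- Middle case, raw: 0.20/(0.2715 × 0.3015) = 2.44, so Φ(0.48) = 0.69.
- Middle case, per kg: 0.20/(0.20 × 0.3015) = 3.32, so Φ(1.36) = 0.91.
- Over the whole grid: 0.44-0.93 raw against 0.60-0.99 per kg.

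**Step 4: what a mass covariate recovers.** Under the same assumptions the variance left after adjusting for mass is CVk²(1 + CVm²). In the middle case this is 0.04 × 1.0324 = 0.0413, so inflation falls from 1.84 to 1.03. A covariate therefore recovers nearly all that the ratio would.

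**Step 5: false positives.** 20,000 three-arm trials were simulated with no true difference (CVm 0.18, CVk 0.20, 22 per arm, one-way ANOVA on raw calories).
- Overall rejection rate: 0.052
- Mass range across arms above 10% (16% of trials): 0.18
- Mass range above 15% (1.7% of trials): 0.40
- Mass range below 5%: 0.013

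**Step 6: would the planned ANCOVA catch it?** If an observed baseline difference means a significant one, then at CVm 0.18 a two-arm imbalance below about 11% (the 10.6% limit in step 1) would usually not trigger it. Even when triggered, body mass need not be the covariate chosen.

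**The case against.** The strongest reply is that little depends on this variable. Borg ratings are the stated measure of session intensity. The calorie sentence goes on to list time in activity bands, and neither is expressed in calories. Total calories could also be read as volume, which the second objective covers too. This stands as a limit on importance, although the section is headed and introduced as intensity control.

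The calculation rests on assumptions. The article gives no SD, and the calories are accelerometer estimates from software whose dependence on mass is not described. Proportionality is therefore unverified, and this is why a range is shown. A ratio can over-correct if proportionality fails. It also leaves session duration and sex in the measure. This argues for the covariate over the ratio.

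A condensed article may leave normalisation to a fuller document. If that document already adjusts for mass, the point falls. The article does, however, name the analysed variable and the adjustment rule, and neither includes mass.

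Three stronger readings are tempting and are not supported:
- A reader might infer that daily calories share the problem. The abstract says all outcomes are assessed at baseline and week 12, so the group-by-period contrast removes most of the stable mass effect.
- A reader might infer that the test is biased. Randomisation keeps the overall error near 0.05; the excess arises only in trials with a large realised imbalance.
- A reader might infer that the protocol contradicts its own practice for strength. Only peak torque, one of three strength variables, is divided by body weight, so there is no consistent rule to breach.

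**Conclusion.** The concern holds for session calories as a loss of precision. Under the assumed CVs, 22 per arm is worth about 8 to 19 per arm on a mass-adjusted scale, and about 12 in the middle case. Chance imbalance in mass also enters the realised contrast, and the planned conditional ANCOVA gives only partial cover.

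The size rests on three things the documents do not supply: the CV ranges, proportionality of calories to mass, and independence of mass and kcal/kg. If the calorie estimate depends less on mass, the loss is smaller. The document does not support saying that calories alone would decide the intensity comparison. This is a worthwhile minor improvement to a secondary process measure.

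**What to change.** State that session calories will be compared between arms in a model with baseline body mass as a prespecified covariate, fitted whether or not the arms are seen to differ. If proportionality is accepted, kcal/kg per session is an alternative. Report raw session calories descriptively. Daily calories need no change on this account.

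No new measurement should be needed: anthropometry is taken at the first visit, and body weight is required for peak torque/body weight. The covariate costs one error degree of freedom (with all 66 analysed, 66 − 3 = 63 becomes 62). The ratio costs no degree of freedom but risks over-correction. The sample size is unaffected.
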